## Abstract

Mitochondrial neurogastrointestinal encephalomyopathy (MNGIE) is an autosomal recessive disorder which primarily affects the gastrointestinal and nervous systems. This disease is caused by mutations in the nuclear *TYMP* gene, which encodes for thymidine phosphorylase, an enzyme required for the normal metabolism of deoxynucleosides, thymidine, and deoxyuridine. The subsequent elevated systemic concentrations of deoxynucleosides lead to increased intracellular concentrations of their corresponding triphosphates, and ultimately mitochondrial failure due to progressive accumulation of mitochondrial DNA (mtDNA) defects and mtDNA depletion. Currently, there are no treatments for MNGIE where effectiveness has been evidenced in clinical trials. This Phase 2, multi-centre, multiple dose, open label trial without a control will investigate the application of erythrocyte-encapsulated thymidine phosphorylase (EE-TP) as an enzyme replacement therapy for MNGIE. Three EE-TP dose levels are planned with patients receiving the dose level that achieves metabolic correction. The study duration is 31 months, comprising 28 days of screening, 90 days of run-in, 24 months of treatment and 90 days of post-dose follow-up. The primary objectives are to determine the safety, tolerability, pharmacodynamics, and efficacy of multiple doses of EE-TP. The secondary objectives are to assess EE-TP immunogenicity after multiple dose administrations and changes in clinical assessments, and the pharmacodynamics effect of EE-TP on clinical assessments.

## 1. Introduction

Mitochondrial neurogastrointestinal encephalomyopathy (MNGIE) is a fatal and rare autosomal recessive disorder of nucleotide metabolism caused by mutations in the nuclear thymidine phosphorylase gene (*TYMP*), which encodes cytosolic thymidine phosphorylase, the enzyme required for the normal metabolism of pyrimidine deoxynucleosides, thymidine, and deoxyuridine [1,2]. Pathogenic variants in *TYMP* result in a complete or partial absence of thymidine phosphorylase activity (<10% of healthy unaffected individuals), leading to an accumulation of thymidine and deoxyuridine in tissues and body fluids [3,4,5,6,7,8,9].

Elevated systemic concentrations of these deoxynucleosides lead to increased intracellular concentrations of their corresponding triphosphates. This perturbs the physiological equilibrium of the deoxynucleoside triphosphate pools within the mitochondria, thereby interfering with the normal replication of mitochondrial mtDNA, leading to multiple deletions, somatic point mutations and depletion of mtDNA [5,8,10,11], and ultimately mitochondrial failure [5,6,8]. It is believed that the consequent failure of cellular energy production directly causes the cardinal clinical manifestations through damage to the nervous and muscular systems.

Patients with MNGIE usually present during the second decade of life, although patients have presented as early as five months and as late as the fifth decade; the average age at diagnosis is 18.5 years [12]. The relatively late onset for a condition present at birth is thought to be due to the progressive accumulation of mtDNA defects, with the disease becoming apparent once the number of affected mitochondria reaches a critical threshold level. The disease is a multi-system disorder, and has a characteristic, although by no means universal, clinical presentation. Patients typically present with gastrointestinal symptoms including early satiety, nausea, dysphagia, gastroesophageal reflux, postprandial emesis, episodic abdominal pain, episodic abdominal distention, and diarrhoea. These symptoms are secondary to alimentary dysmotility caused by degeneration of the alimentary autonomic nervous system [2]. Patients generally have a thin body habitus with reduced muscle mass and cachexia. Episodes of frank intestinal pseudo obstruction may occur, and some patients develop a hepatopathy with liver steatosis and cirrhosis. Progressive external ophthalmoplegia and peripheral sensorimotor polyneuropathy are invariable. The latter affects the lower limbs initially and is typically demyelinating. On magnetic resonance imaging (MRI) there is, in the majority of cases, leukoencephalopathy with diffuse increased T2 signal in the deep white matter of the cerebral hemispheres, but this is generally believed to be asymptomatic [5,12].

MNGIE is a progressive disease, with patients dying at an average age of 37.5 years, and at present there are no approved therapies [4]. Allogeneic hematopoietic stem cell transplantation (HSCT) offers the possibility of a permanent correction of the thymidine phosphorylase deficiency. However, it is still highly experimental, carrying a mortality rate of approximately 63% [13]. Treatment with allogeneic HSCT is limited by the availability of a matched donor, and patients are often in poor clinical condition with impaired capacity to tolerate transplant related problems and the aggressive conditioning and immunosuppressive chemotherapy [13,14]. The administration of HSCT to patients with MNGIE presents pharmacological challenges in terms of administering drugs with possible mitochondrial toxicity, and the requirement for parenteral administration due to disturbed gastrointestinal function and impairment of absorption. A published consensus proposal for standardising an approach to allogeneic HSCT in patients with MNGIE recommends restricting the recruitment of patients with an optimal donor to those without irreversible end stage disease [13,14]. Patients who are oligosymptomatic are often reluctant to undergo HSCT due to its high mortality risk. Many patients are therefore ineligible for this treatment option and clinical management is based on symptom relief and palliation. A second experimental permanent treatment approach for MNGIE is orthotopic liver transplantation. Sustained normalisation of plasma thymidine and deoxyuridine concentrations have been reported in two patients who received liver transplantation [15]. A longitudinal evaluation of additional transplanted patients, however, is essential to confirm the clinical efficacy of this treatment approach. There is thus a critical requirement to develop an alternative treatment for these patients which would provide an expeditious normalization of nucleosides to prevent as much mitochondrial damage as possible.

The Investigational Medicinal Product under investigation in this study is erythrocyte encapsulated thymidine phosphorylase (EE-TP), which is produced under Good Manufacturing Practice by the ex vivo encapsulation of recombinant *Escherichia coli* thymidine phosphorylase into patient’s autologous erythrocytes using an automated red cell loader device [16]. EE-TP is intravenously infused into the patient where it aims to correct the fundamental lesion in MNGIE by replacement of the deficient thymidine phosphorylase. The rationale for the development of EE-TP is based on thymidine and deoxyuridine being able to diffuse across the erythrocyte membrane via nucleoside transporters into the cytosol where the encapsulated enzyme catalyses their metabolism to the normal products, thymine and uracil, respectively (Figure 1). The products then exit the cell into the blood plasma where they are further metabolised as normal. It is proposed that regular intravenous (IV) administrations of EE-TP to patients with MNGIE will lead to a sustained reduction or elimination of plasma thymidine and deoxyuridine, leading to a clearance from the cellular compartments and thus an amelioration of the intracellular deoxynucleotide imbalances. This should prevent further damage to mtDNA. By relieving the nervous system and muscle of the toxic effects of the accumulated metabolites, EE-TP aims to arrest and reverse the progression of the clinical disease.

EE-TP has the advantage of prolonging the circulatory half-life of the enzyme to that of the erythrocyte half-life (19–29 days) and minimising immunogenic reactions, which are often observed in enzyme replacement therapies administered by the conventional route.

Clinical experience with EE-TP is limited to a proof-of-concept study in a single patient diagnosed with MNGIE and a compassionate clinical evaluation in four patients with MNGIE [17,18,19]. EE-TP was well tolerated and reductions in the disease-associated plasma metabolites, thymidine and deoxyuridine, were observed in all patients. Clinical improvements were observed in three patients who received long-term treatment, suggesting that EE-TP is able to reverse some aspects of the disease pathology. Transient, non-serious adverse events were observed in two of the five patients; these did not lead to therapy discontinuation and were managed with pre-medication prior to infusion of EE-TP. Despite using an *E. coli* recombinant protein, specific anti-thymidine phosphorylase antibodies were detected in only one patient.

The aim of this study is to investigate the safety, tolerability, pharmacodynamics, and efficacy of EE-TP in patients with MNGIE. We hypothesise that treatment with EE-TP will arrest and reverse the progression of the clinical disease. The study protocol reported here (version 6.0) was written in compliance with the Standard Protocol Items: Recommendations for Interventional Trials (SPIRIT) 2013 [20]. The sponsor, St George’s, University of London, requested scientific assistance for EE-TP and the current protocol was updated in line with the European Medicines Agency (EMA) advice provided. The study will be conducted in accordance with the following and all subsequent amendments: (i) International Council for Harmonisation of Technical Requirements for Registration of Pharmaceuticals for Human Use (ICH) E6: Good Clinical Practice: Consolidated guideline Committee for Proprietary Medicinal Products (CPMP)/ICH/135/95 (July 1996), adopted in the EU by CPMP, (ii) European Commission Directive 2001/20/EC (April 2001), (iii) European Commission Directive 2003/94/EC (October 2003), (iv) European Commission Directive 2005/28/EC (April 2005), (v) Manufacture of Investigational Medicinal Products: Volume 4, Annex 13 of the EU Guidelines to Good Manufacturing Practice (February 2010), and (vi) The Medicines for Human Use (Clinical Trials) Regulations 2004 and all subsequent amendments.

## 2. Methods

### 2.1. Trial Objectives

The primary objectives of this study are to determine the safety, tolerability, pharmacodynamics, and efficacy (as measured by weight stabilisation) of multiple doses of EE-TP in patients with MNGIE. The secondary objectives are to assess the immunogenicity of EE-TP after multiple dose administrations, evaluate changes in clinical assessments, and assess the pharmacodynamics effect of EE-TP on clinical assessments. Additional exploratory objectives aim to evaluate the effects of EE-TP on serum and plasma markers of mitochondrial condition, MRI (brain), abdominal ultrasound, electromyography, and neuro-ophthalmological assessments.

### 2.2. Study Drug

EE-TP will be prepared by trained personnel using an automated red cell loading process at each trial site according to the Red Cell Loader protocol. A predetermined volume of the patient’s blood (120 to 360 mL) will be removed from the patient and then introduced into the Red Cell Loader, which separates the blood components and then subjects the erythrocytes to a reversible hypo-osmotic dialysis process. Under hypo osmotic conditions, the erythrocytes swell due to an influx of water and at a critical size, pores form in the membrane. Whilst in a permeable state, the study drug, thymidine phosphorylase, enters the erythrocytes by diffusion. The permeability was reversed by restoration of iso-osmotic conditions, encapsulating the thymidine phosphorylase within the erythrocytes, to form EE-TP. The EE-TP will be dispensed into a sterile European Pharmacopoeia grade 100 mL capacity blood transfer bag and released as multiple units (2–6 bags, the number depending on the dose to be administered) for infusion within 30 min of manufacture. Characteristics of EE-TP are shown in Table 1.

### 2.3. Trial Design

The trial is a Phase 2, multi-centre, multiple dose, open label trial without a control which will be conducted in a maximum of five sites in Europe and Israel, with all patients receiving EE-TP. For each patient, the overall study duration will be 31 months, consisting of a 28 day screening phase, a 90 day run-in phase, a 24 month open-label treatment phase, and a 90 day follow-up phase. A schematic of the proposed study design is presented in Figure 2.

Patients will be screened for eligibility from Day −120 to Day −92. If eligible, patients will then enter the run-in period, from Day −91 to pre-dose on Day 0, in which key aspects of their overall clinical condition and metabolite levels will be recorded. The variability in these clinical and metabolic parameters is currently unknown, and these data will primarily serve to act as each patient’s own pre-treatment/control observations.

Prior to entering the treatment phase, patients will attend the study site for pre-treatment assessments and to determine continued study eligibility either the day before dosing (Day –1) or in the morning of the day of dosing (Day 0). For the first four treatment cycles, the administration will be every 21 days, with the administration of EE-TP at the same time of day (±2 h). The first dose (Treatment Cycle 1) of EE-TP will be administered on day 0, with subsequent doses on Days 21, 42, and 63 (Treatment Cycles 2, 3 and 4, respectively). For Treatment Cycles 1, 2, 3, and 4, patients will leave the study site following dosing and return the next day (Days 1, 22, 43, and Day 64, respectively) for 24 h post-dose assessments. The planned dose levels are presented in Table 2. All patients will receive infusions at Dose Level 1 (~58–65 × 10^10^ erythrocytes encapsulating ~30–49 U TP/10^10^ erythrocytes) for the first 2 treatment cycles (Treatment Cycles 1 and 2). If metabolic correction (defined as plasma thymidine <3 µmol/L and deoxyuridine <5 µmol/L, i.e., below the diagnostic levels for MNGIE) is not achieved, the subsequent 2 treatment cycles (Treatment Cycles 3 and 4) will be administered at Dose Level 2 (~58–65 × 10^10^ erythrocytes encapsulating ~50–69 U TP/10^10^ erythrocytes).

From Day 78, the dose will remain at the dose that achieved metabolic correction during the initial treatment phase (pre-Day 78). If metabolic correction was not achieved, treatment will advance to Dose Level 3 (~58–65 × 10^10^ erythrocytes encapsulating ~70–90 U TP/10^10^ erythrocytes) for subsequent treatment cycles. It is planned that patients will receive EE-TP every 2–4 weeks ± 2 days until the end of the study. Dose frequency may be reduced (e.g., from every 2 weeks to every 3–4 weeks) for individual patients based on emerging safety, tolerability, efficacy, and pharmacodynamics data. The interval between doses will not be shorter than 2 weeks ± 2 days. In the advent of an increase in plasma metabolite levels, the frequency of dosing and/or dose level will be reviewed and adjusted accordingly.

The study will be flexible; continued pharmacodynamic assessment will enable dose optimisation and further inform dose response models and establish the therapeutic window for the treatment. A Patient Oversight Committee will perform ongoing reviews of safety, tolerability, efficacy, and available pharmacodynamic data to ensure the acceptability of continued dosing and/or dose progression for each patient. An overview of the dosing scheme is presented in Figure 3.

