### 2.5. Interventions

#### 2.5.1. Preparation and Administration of Erythrocyte Encapsulated Thymidine Phosphorylase (EE-TP)

On the morning of each treatment cycle patients will undergo venesection for the collection of 120–360 mL of blood for the manufacture of EE-TP. The volume of blood collected will be dependent on the patient’s haematocrit, red cell count, and the dose of EE-TP to be administered. EE-TP will be administered as an intravenous infusion, within 30 min of the completion of manufacture, according to the specified study protocol, using a standard intravenous infusion set with a micro-aggregate filter in-line. 

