#### 2.8.1. Safety Data Analysis

A baseline sign and symptom will be defined as an adverse event that starts after the patient has provided written informed consent and resolves prior to the first treatment cycle. It will also be defined as an adverse event that starts prior to the first treatment cycle and does not increase in severity after dosing. A treatment emergent adverse event will be defined as an adverse event that occurs post-dose or that is present pre-dose and becomes more severe post-dose. Treatment emergent adverse events will be summarised by dose level, maximum severity, and relationship to the study drug. The frequency of treatment emergent adverse events plus the number and percentage of patients experiencing a treatment emergent adverse event will be summarised by dose level, the Medical Dictionary for Regulatory Activities system organ class, plus preferred term. A frequency summary will be presented by day of onset across the multiple dosing period. 

Vital signs, serum biochemistry, haematology, and urinalysis data will be summarised by dose level, together with changes from the baseline. All serum biochemistry, haematology, and urinalysis data outside the clinical reference ranges will be listed by parameter and treatment. ECG data, including QTc, QTcB, QTcF, the PR and QT intervals, QRS duration, and heart rate, will be obtained directly from the 12-lead ECG traces. The ECG data will be summarised by dose level. Values for ECG parameters outside the clinical reference ranges will be indicated on the individual patient data listings. Physical examination and concomitant medication data will be listed.

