Neurological examination		X		X
MRI (brain)		X		X
Abdominal ultrasound		X		X
Nerve conduction and electromyography ^5^		X		X
Neuro-ophthalmological assessment		X		X
FGF-21, GDF15, and other markers of mitochondrial condition		X		X

^1^ For adult patients, height will be measured at the beginning of run-in period. For juvenile patients, height will be measured with weight at all time points. ^2^ Female patients only; pregnancy test at Day 0 (Treatment Cycle 1) to be conducted prior to study drug administration. ^3^ Serum biochemistry: Alanine aminotransferase, aspartate aminotransferase, alkaline phosphatase, albumin, gamma glutamyl transferase, sodium, potassium, chloride, calcium, magnesium, inorganic phosphate, glucose (non-fasting), urea, uric acid, total bilirubin, direct bilirubin, creatine kinase, iron, ferritin, folate, vitamin b12, total protein, cholesterol (including total, low density lipoprotein, and high density lipoprotein), triglycerides, lactate dehydrogenase, c reactive protein, and creatine kinase. Haematology: white blood cell count, red blood cell count, red cell distribution width, haemoglobin, haematocrit, mean cell volume, mean cell haemoglobin, mean cell haemoglobin concentration, platelet count, white blood cell differential, international normalised ratio, CD4+, and CD8+. ^4^ At screening the investigator and patient will identify the patient’s most disabling symptom. ^5^ Sensory bilateral nerves: Median, ulnar, radial, sural, and superficial peroneal; motor bilateral nerves: Median, ulna, common peroneal, and post tibial; EMG: Dorsal interosseous, tibialis anterior, and gastrocnemius bilateral muscles.

**Table 4 jcm-08-01096-t004:** Schedule of assessments during the treatment and follow-up phases.

Assessment	Study Day																	
	0 TC 1	1	7	14	21 TC 2	22	28	35	42 TC 3	43	49	56	63 TC 4	64	70	77	Every 2–4 Weeks up to 24 Months	Follow-Up 90 Days Post-Dose
Pregnancy test ^1^	X						X					X					X	X
RBC count					X				X								X	
Administration of Study Drug	X				X				X			X					X	
Adverse event recording	Ongoing during the study																	
Concomitant medication ^2^	Ongoing during the study																	
Vital signs	X	X			X	X			X	X			X	X	X	X	X	X
12-lead ECG	X	X			X	X			X	X			X	X	X	X	X	X
Clinical laboratory evaluations ^3^	X		X		X	X									X	X	X	X
Physical examination					X										X	X	X	X
Anti-TP antibody/neutralising antibodies	X								X				X				X	X

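### Table 4 marks the fourth dose at Day 56 against Day 63 in Section 2.3, and its laboratory and red-cell rows leave gaps around cycles 3 and 4

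*Protocol article*

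**What the plan says.** **Dosing days.** Section 2.3 states: "For the first four treatment cycles, the administration will be every 21 days". It gives the first dose on Day 0, "with subsequent doses on Days 21, 42, and 63 (Treatment Cycles 2, 3 and 4, respectively"), and has patients "return the next day (Days 1, 22, 43, and Day 64, respectively) for 24 h post-dose assessments". The Figure 2 caption repeats the 21-day interval. The header of Table 4 labels Day 63 as TC 4. In the row "Administration of Study Drug", however, the fourth mark is under Day 56 and the Day 63 cell is empty.

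**Laboratory tests.** Section 2.5.3 leaves the timing of blood and urine samples to Tables 3 and 4. In Table 4 the row "Clinical laboratory evaluations" is marked at Days 0, 7, 21, 22, 70 and 77, at the later 2- to 4-weekly visits and at follow-up. Section 2.6.2 makes the incidence of laboratory abnormalities a safety endpoint, and Section 2.8.1 adds: "Vital signs, serum biochemistry, haematology, and urinalysis data will be summarised by dose level".

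**Red-cell inputs.** Section 2.5.1 has blood drawn on the morning of each cycle, in a volume that depends on the patient's "haematocrit, red cell count, and the dose of EE-TP to be administered". The red-cell row of Table 4 is marked at Days 21 and 42 and at the later visits. The table has no separate haematocrit row.

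**The concern.** Table 4 is the schedule from which visits would be run, and it disagrees with the text on a dosing day. A site that took the study-drug row literally would give cycle 4 a week early, on a day with no vital signs or ECG marked. There is no Day 57 column for the 24-hour visit that the Conclusions cite among the safety provisions for the first four doses. The Day 63 efficacy assessments of Section 2.6.1, and the Day 63 metabolite sample, would then fall 7 days after a dose instead of on the dosing day.

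The laboratory blanks fall where the dose may first be raised. Safety is a primary objective and laboratory data are to be summarised by dose level, yet no full panel is scheduled between the first and second infusions at Dose Level 2. At cycle 4 the schedule also does not supply current values of two of the quantities on which Section 2.5.1 makes the venesection volume depend.

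**Working it through.** **1. The plan's own dosing days.** Start on Day 0 with a 21-day interval (Section 2.3): 0, 0 + 21 = 21, 0 + 2 × 21 = 42, 0 + 3 × 21 = 63. This reproduces the text, and the 24-hour visits at Days 1, 22, 43 and 64 agree with it.

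**2. Table 4, cell by cell.** The header has 18 columns: 16 study days, the 2- to 4-weekly visits and follow-up. Each row below also has 18 cells.

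| Row | Columns marked | Days |
|---|---|---|
| Study drug | 1, 5, 9, 12, 17 | 0, 21, 42, **56**, later visits |
| Vital signs and ECG | 1, 2, 5, 6, 9, 10, 13–18 | 0, 1, 21, 22, 42, 43, **63, 64**, 70, 77, later visits, follow-up |
| Clinical laboratory | 1, 3, 5, 6, 15–18 | 0, 7, 21, 22, 70, 77, later visits, follow-up |
| Red-cell count | 5, 9, 17 | 21, 42, later visits |
| Pregnancy test | 1, 7, 12, 17, 18 | 0, 28, 56, later visits, follow-up |

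**3. Could the mark at Day 56 come from text extraction?** This is unlikely. The study-drug row has all its cells, and its last mark falls correctly under the later visits. The pregnancy row gives Days 0, 28 and 56, which fits its four-weekly footnote, so the Day 56 column is in place. Vital signs and ECG fall on Days 63 and 64, so those columns are in place too.

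**4. Dosing interval, cycle 3 to cycle 4.** Text: 63 − 42 = 21 days. Table: 56 − 42 = 14 days. Difference: 7 days.

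**5. Laboratory gap.** The blank columns are Days 28, 35, 42, 43, 49, 56, 63 and 64, eight in all. The distance between marked days is 70 − 22 = 48 days. From the Day 42 infusion to the next panel is 70 − 42 = 28 days. Day 70 is 70 − 63 = 7 days after cycle 4 by the text, or 70 − 56 = 14 days by the table. On either reading it follows the second possible Dose Level 2 infusion. Cycle 2, at Dose Level 1, has a panel on the dosing day and the next day; cycles 3 and 4 have neither.

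**6. Contribution to the summary by dose level.** A patient not corrected at Dose Level 1 receives Dose Level 2 at cycles 3 and 4. If still not corrected, the patient moves to Dose Level 3 from Day 78. The scheduled panels in between are Days 70 and 77, so there are two.

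**7. Red-cell inputs at cycle 4.** The last scheduled red-cell count is Day 42, which is 63 − 42 = 21 days earlier by the text or 56 − 42 = 14 by the table. Haematocrit is part of the haematology panel (Table 3, footnote 3), so its last scheduled value is Day 22. That is 63 − 22 = 41 or 56 − 22 = 34 days earlier.

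**The case against.** The strongest reply is that the Day 56 mark is a misprint in one cell. The text, the 21-day interval, the Day 64 visit, the Figure 2 caption, the table's header and its vital-sign, ECG and antibody rows all indicate Day 63. A site would have to overlook the TC 4 heading to dose on Day 56. The document is also a journal article, and the full protocol may not carry the error. This makes actual misdosing improbable. It does not remove the contradiction, which is in the one row that says when drug is given.

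On the laboratory row, nothing in the article promises a panel at every cycle, and the interval is not unmonitored. A red-cell count is marked at Day 42, vital signs and ECG at Days 42, 43, 63 and 64, antibodies at Days 42 and 63, and metabolites throughout. That is fair, and the blanks may be intended. But none of these supplies biochemistry, full haematology or urinalysis, and the article does not reconcile the blanks with its summary by dose level.

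Three stronger readings are tempting, and the document does not support them:

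- *All Dose Level 2 laboratory data come from Days 70 and 77.* Section 2.3 keeps patients on the dose that corrected them, so those corrected at Dose Level 2 contribute panels at later visits for the rest of treatment.
- *The Patient Oversight Committee would judge dose steps without laboratory data.* Panels at Days 0, 7, 21 and 22 precede the possible step at Day 42, and those at Days 70 and 77 precede the step from Day 78. What is missing is any full panel at Dose Level 2 before the second infusion at that level.
- *The venesection maxima over the two cycles add up to a blood loss.* The erythrocytes are the patient's own and are reinfused, so the sum is not a net loss.

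The red-cell omission is also narrow. Table 3 covers cycle 1 and the later-visit column covers cycles after the fourth, so for the count itself only cycle 4 is unmarked. Section 2.5.1 does not say how recent the values must be.

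**Conclusion.** The point holds in a limited form. Table 4 contradicts Section 2.3 and its own heading on the day of the fourth dose, by 7 days. The laboratory row has no mark from Day 28 to Day 64. For patients escalated at cycle 3, the first scheduled panel therefore comes 28 days after the first Dose Level 2 infusion and after the second. Those not corrected at Dose Level 2 contribute only Days 70 and 77 to that level's laboratory summary. At cycle 4 no red-cell count is marked, and the last scheduled haematocrit is 41 days old by the text (34 by the table).

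This rests on four assumptions:

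- The printed table matches the extracted cells, which the row checks support.
- The Table 4 panel is the one listed under Table 3, because footnote 3 of Table 4 refers back to Table 4 itself.
- A laboratory value counts towards the dose level last infused. A pre-dose sample at the first Dose Level 3 visit could, under that rule, add one more value to Dose Level 2.
- The dose is not later reduced to Dose Level 2 under the flexible dosing.

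How many patients are affected is unknown, since the article does not say what share should need Dose Level 2. Because the table governs both dosing visits and sample timing, it should be corrected before the first patient is enrolled.

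**What to change.** Reconcile the study-drug row of Table 4 with Section 2.3 and with the table's own column headings, and check that the vital-sign, ECG, red-cell, metabolite and Day 63 efficacy marks all refer to the confirmed day. Reconcile the laboratory and red-cell rows for cycles 3 and 4 with Section 2.5.1 (inputs to the venesection volume), Section 2.6.2 (laboratory safety endpoint) and Section 2.8.1 (summary by dose level). If the blanks are intended, the document should say so and state what the Dose Level 2 laboratory summary will then contain. Which dosing day and which sampling schedule are right is for the sponsor to state.

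The cost is a correction to one table, with an amendment if the full protocol carries the same entries. Section 2.13 says that recruitment has not opened, so no collected data are affected. Should the sponsor find that marks are missing, plasma is already drawn at Days 42, 49, 56 and 63, so few or no new visits would be needed.
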